#### Other Health Behaviors

Nineteen questions were included in the surveys to assess the other health behaviors addressed in the social media program. Participants rated their overall health status as excellent to poor. They described their diet by reporting the number of servings of fruits and of vegetables eaten each day and the number of times they drank regular soda or pop that contained sugar or sugar sweetened drinks (not 100% fruit juice or diet/artificially sweetened) in the past 30 days. Body mass index was calculated by asking for height (in inches) and weight (in pounds). Participants also described their regular physical activity, indicating how many times they engaged in vigorous and in light or moderate activities for at least 10 minutes per week. Alcoholic beverage intake was assessed by both number of days consuming at least 1 alcoholic drink in the past 30 days and number of times 4 or more alcoholic drinks were consumed in a row (binging) in the past 2 weeks was reported, along with smoking behavior (ie, smoking history; smoked at least 100 cigarettes in their lifetime) and current smoking (currently smoke every day, some days, or not at all). Mental health was assessed by asking how many days in the past 30 days was their mental health not good and disability was measured as the number of days in the past 30 days when poor physical or mental health kept them from doing their usual activities. Compliance with human papillomavirus (HPV) vaccination advice was assessed by asking if the daughter had been vaccinated and if so how many shots she received. Finally, 2 items measured abuse of prescription drugs: have you ever or in the past 6 months used a drug that was not prescribed for you or that you took only for the experience or feeling it caused even once? 

#### Engagement

Mothers’ engagement (ie, number of posts, comments, likes, and views with the *Health Chat* program) will be extracted from the Facebook page using a computer program.

Maternal communication will be assessed using 8 items asking mothers if they have talked to their daughters about indoor tanning in the past year. For example, “Within the past year, I have talked with my daughter about the importance of not being pressured to go to the tanning bed to fit in.” Response options will include “yes,” “no,” and “I prefer not to answer.” Mother-daughter relationship quality will be assessed using 2 Likert-type items (1=strongly disagree, 5=strongly agree): “I let my daughter make her own decisions,” and “Overall, I am satisfied with the way my daughter and I communicate.” Daughters will be asked the same 2 items to assess their perceptions of relationship quality. At the end of intervention follow-up (1-year), mothers will also be asked about how they shared information from the Facebook group with their daughter (eg, showed daughter a post in the private group).

### Analysis Plan

Hypotheses will be tested using a multilevel (mother-daughter dyad nested in Facebook private group) structural equation model (SEM). The following specific tests within the multilevel SEM will be used to evaluate the primary hypotheses in order to examine the effects of the social media campaign on indoor tanning outcomes. For the hypothesis regarding mothers’ permissiveness for daughters to indoor tan, mothers’ permissiveness (a level 1 variable) will be specified as a multiple indicator latent construct and regressed on the treatment indicator (campaign with prescription drug messages (control) vs campaign with indoor tanning messages (intervention), a level 2 variable). Similarly, for the hypothesis regarding daughters’ perceptions of mothers’ permissiveness, daughters’ perceptions (a level 1 variable), a multiple indicator latent construct, will be regressed on the treatment indicator (a level 2 variable). Mother and daughter perceptions will be correlated. In testing the hypothesis relating to indoor tanning frequency, mothers’ and daughters’ tanning (level 1 variables) will be specified as a count of the number of tanning sessions (in the past 3 months) and regressed on the treatment indicators (a level 2 variable), using a zero-inflated negative binomial distribution (which simultaneously models the effect of the intervention on the prevalence and frequency (among tanners) of tanning sessions). Mother and daughter behavior will be correlated. Finally, the hypothesis relating to mothers’ support for IT bans will be tested by regressing mothers’ signatures on the Web-based petitions (a level 1 binary variable—signed or not signed) on the treatment indicator (a level 2 variable) in a multilevel SEM.

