### Study Design

The study design is a randomized controlled trial comparing 2 conditions over 1 year (Figure 1). Participants will be recruited in waves of approximately 84 and then randomized into the intervention or control condition. We continue in this way until a total of 25 waves have been enrolled, producing 25 groups in the intervention condition and 25 groups in the control condition each with approximately 42 participants. Participants will be blinded to condition and assessment points will occur at baseline, end of intervention (1-year), and 6 months postintervention.

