We used the Optimal Design software package (version 3.0) [45] to determine sample size. Assuming a 2-tailed alpha of 0.05, a moderate effect size of d=0.50, and an intraclass correlation of 0.05 within each Facebook private group, we far exceed a power of 0.80 with 50 Facebook private groups each consisting of 25 mothers (total n=1250 mothers and 1250 daughters). We increased this sample size to account for the proportion of minority mothers and daughters (15%) we expect to recruit to achieve the needed sample size of non-Hispanic whites, the racial/ethnic group most likely to indoor tan and with the highest rates of melanoma [40]. We further inflated the sample to account for an expected loss to follow-up of 30% by 12 months (20% at 6 months). Thus, we will recruit initial samples of 2100 mothers and 2100 daughters (42/Facebook group) at baseline and expect to successfully assess 1680 in each sample (approximately 34/Facebook group) at the 6-month follow-up and 1470 in each sample (approximately 29/Facebook group) at the 12-month follow-up, with the final samples containing 1250 non-Hispanic white mothers and 1250 non-Hispanic white daughters for analysis.

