#### Primary Outcomes

Mothers’ permissiveness for daughters to tan indoors will be assessed using 4 Likert-type items (1=strongly disagree, 5=strongly agree) assessing permissiveness toward their teenage daughters’ indoor tanning [79]. Example items include, “I would allow my daughter to indoor tan,” and “I think it’s OK for my daughter to indoor tan” (Cronbach alpha=.97). Daughters will be asked the same 4 items to assess their perceptions of mothers’ permissiveness (Cronbach alpha=.95) [46]. Maternal permissiveness will be assessed at baseline and both follow-ups by the combined average ratings across the 6 items.

Indoor tanning behavior will be assessed by asking mothers and daughters to report on their indoor tanning over the last year using a single open-ended item (ie, “How many times in the past year have you used a tanning bed or booth?”) [80] Similar measures had strong positive correlations with diary measures of indoor tanning behavior (*r*=.77-.86, *P*<.001) in previous work [81,82]. Intention to indoor tan will also be assessed (ie, How likely is it that you will indoor tan in the next 3/6/12 months; 7-point Likert response scale), along with intention to get a sunless tan (eg, self-tanners, spray tans) in the next 12 months. We also will include an item specific to the months of December-March to capture indoor tanning during the seasonally high months of indoor tanning use. Indoor tanning behavior and intentions will be assessed at baseline and both follow-ups.

Support for strengthening bans on indoor tanning by minors will be measured via the Web server, which will record whether mothers who click on the link to “sign” the petition to strengthen the ban on indoor tanning and forward it to their legislator. At the final follow-up, mothers will be asked how much they support bans on indoor tanning by minors and about their reasons for either signing or not signing the petition.

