#### Seasonality Issues

In order to account for the issue of seasonality (ie, that indoor tanning is more common during certain times of the year), we will measure indoor tanning at each follow-up, asking specifically about tanning during the months of December-March. We will also include date of measurement as a covariate.  We will control for month of assessment and number of months that have elapsed since baseline. In addition, the treatment and control group, randomized together, will be surveyed at precisely the same times to ensure equivalency.

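### The stated primary models name date and month covariates but neither the baseline outcome nor the randomisation wave, which costs precision though not validity

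*Protocol article*

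**What the plan says.** All references are to the protocol article.

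- **Analysis Plan.** Hypotheses are tested in a multilevel structural equation model with two levels, dyad and Facebook group. Mothers' permissiveness is "specified as a multiple indicator latent construct and regressed on the treatment indicator". Daughters' perceptions, the tanning counts and the petition signature are likewise regressed on treatment. This section names no covariates.
- **Seasonality Issues.** Date of measurement is a covariate, and "We will control for month of assessment and number of months that have elapsed since baseline". The two arms of a wave are to be surveyed at the same times.
- **Study Design.** "Participants will be recruited in waves of approximately 84 and then randomized into the intervention or control condition". This is repeated for 25 waves, giving 25 groups per arm, one of each from every wave.
- **Primary Outcomes.** "Maternal permissiveness will be assessed at baseline and both follow-ups". Indoor tanning is also measured at baseline. The petition signature has no baseline counterpart.

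**The concern.** Two pieces of information that the design creates are not used in the models as stated.

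First, a person's permissiveness or tanning at baseline usually predicts the same measure later. Leaving it out keeps explainable variance in the residual.

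Second, each wave supplies one group to each arm, so anything shared within a wave cancels from the treatment contrast. Such shared features include season, recruitment source, and location as the staff sweep across the region. A model that treats the 50 groups as independent given treatment still counts that shared variance in the between-group error. The reported standard error is then too large for the paired design and the test is conservative. Date and month will absorb some of this variance, but they need not capture recruitment source or location.

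What is at stake is the width of the intervals and the power for effects below the planned size.

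**Working it through.** **Inputs from Sample Size and Power Calculations.** "Assuming a 2-tailed alpha of 0.05"; "a moderate effect size of d=0.50"; "an intraclass correlation of 0.05 within each Facebook private group"; and "we far exceed a power of 0.80 with 50 Facebook private groups each consisting of 25 mothers". So J = 50 groups, m = 25, ICC = 0.05.

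**Assumptions (not in the document).** Baseline-to-follow-up correlation r = 0.5 to 0.7. Wave carries half of the between-group variance, and date and month absorb none of it. The formulas are for a continuous outcome with SD 1.

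**1. The plan's own figure.**
SE = sqrt(4 × (ICC + (1 − ICC)/m) / J) = sqrt(4 × (0.05 + 0.038) / 50) = 0.0839.
With 48 df, power at d = 0.50 is 0.9999, so the claim of power well above 0.80 reproduces without any covariate.
Detectable d at 80% power = (2.011 + 0.849) × 0.0839 = 0.240.

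**2. Baseline.** Groups are formed by randomisation, so baseline should vary little between them. I therefore let it explain only person-level variance, which is the cautious choice.
SE ratio = sqrt((0.05 + 0.038 × (1 − r²)) / 0.088).

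| r | SE ratio | Reduction |
|---|---|---|
| 0.5 | 0.944 | 6% |
| 0.6 | 0.919 | 8% |
| 0.7 | 0.888 | 11% |

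If baseline explained between-group variance equally well, the ratio would be sqrt(1 − r²). At r = 0.5 the SE would be 0.0727, a 13% reduction, so the table is a lower bound.

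**3. Wave.** Removing half of the between-group variance gives sqrt((0.025 + 0.038) / 0.088) = 0.846, a 15% reduction. With 24 df, detectable d = (2.064 + 0.857) × 0.0710 = 0.207. If wave carries no variance, the lost degrees of freedom raise detectable d from 0.240 to 0.245.

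Under the same half-share assumption, simulating 25 pairs with no treatment effect shows the conservatism: a nominal 5% unpaired test rejects about 2.2% of the time and the paired test about 5%.

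**4. Both, at r = 0.6.**
SE ratio = sqrt((0.025 + 0.038 × 0.64) / 0.088) = sqrt(0.0493 / 0.088) = 0.749.
SE = 0.0628; detectable d = 2.921 × 0.0628 = 0.183.

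**5. Where it matters.** At d = 0.50 power is at least 0.9999 in every case. At an illustrative d = 0.20 it is 0.65 with no adjustment and 0.86 with both.

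**The case against.** **The models are not treatment-only.** A reader of the Analysis Plan alone might infer that outcomes are regressed on treatment and nothing else. Seasonality Issues contradicts this, and its calendar terms will take up part of any wave effect. The 15% is therefore an upper figure for that assumed share of variance. This objection stands.

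**There is no bias.** A reader might infer that omitting baseline biases the estimate. Under randomisation it does not: chance imbalance averages to zero and the standard error allows for it. The study of mothers cited in the sample-size section can make the risk look larger than it is. There the arms differ by 2.98 − 2.47 = 0.51 at follow-up, but already differed by 3.02 − 2.59 = 0.43 at baseline, leaving a difference in change of 0.08. That example does not carry over, for two reasons:
- It sets raw follow-up against change scores, whereas covariate adjustment gives about d = 0.39, 0.31 and 0.23 at r = 0.3, 0.5 and 0.7.
- Its baseline gap is about 0.41 SD. With baseline ICC near zero, chance imbalance here has an SD of about 2/sqrt(2100) = 0.044, so such a gap is implausible.

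**Planned power is safe.** This also stands. A reader who infers that the trial is underpowered for its planned effect goes beyond the figures.

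**A condensed article may leave covariates to an analysis plan.** This stands in part. An unseen plan may include both terms. But the article does state the models, the levels and a set of covariates, and what it states does not match the paired design.

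**Conclusion.** The point holds as one of efficiency and of matching the analysis to the design. As stated, the primary models use neither the baseline outcome nor the randomisation wave.

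For a continuous outcome, baseline adjustment would reduce the standard error by at least 6 to 11% if r is 0.5 to 0.7. Wave adjustment would reduce it by up to about 15% if half of the between-group variance lies between waves and the calendar covariates remove none of it. The two together could bring the detectable effect from about 0.24 to as low as 0.18 SD. The correlation and the wave share are assumptions, and the figures do not transfer directly to the zero-inflated tanning counts or the binary petition outcome.

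The documents do not support a claim of bias or of inadequate power at d = 0.50.

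**What to change.** 1. Add the baseline value of the same outcome to the permissiveness models (as a latent baseline) and to the tanning models (as the count or log(count + 1)). Leave it out of the petition model, which has no baseline. Handle daughters without a baseline under the imputation that the Recruitment section already plans.
2. Add wave to all primary models, including the petition model, as a random level above Facebook group or as fixed strata where the model can be estimated.
3. Reconcile Analysis Plan and Seasonality Issues into one covariate list per model, and state which calendar terms remain once wave is included.

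**Cost.** No new data are needed, and the change can be made before results are examined. Wave as fixed effects leaves about 24 rather than 48 df, a detectable d of 0.245 against 0.240 if wave turns out to carry no variance. There is also some added complexity: 25 strata across 50 groups may be hard to fit in the latent-variable and zero-inflated models, which favours the random level there.

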### Intervention Condition

In the intervention condition, participants will enter a private Facebook group that posts a feed of health messages in which 25% are focused on preventing indoor tanning and 75% are focused on other health topics (eg, nutrition, physical activity, etc). Indoor tanning increases in December, peaking in March for seasonal tanners (eg, event and regular seasonal tanners) [37,38]. During these months, indoor tanning posts will be scheduled at a higher frequency (30% of posts).

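### Indoor tanning is collected as a past-year count but specified for analysis as a past-3-month count that no described item supplies

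*Protocol article*

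**What the plan says.** Under Measures, Primary Outcomes, mothers and daughters "report on their indoor tanning over the last year using a single open-ended item", worded as "How many times in the past year have you used a tanning bed or booth". The same section places this item at baseline and at both follow-ups. It adds one other behaviour item: "We also will include an item specific to the months of December-March to capture indoor tanning during the seasonally high months of indoor tanning use". Seasonality Issues repeats this: "we will measure indoor tanning at each follow-up, asking specifically about tanning during the months of December-March". The only 3-month wording among the measures looks forward and concerns intention, not behaviour: "How likely is it that you will indoor tan in the next 3/6/12 months".

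The Analysis Plan has mothers' and daughters' tanning "specified as a count of the number of tanning sessions (in the past 3 months"), regressed on treatment with a zero-inflated negative binomial distribution. It does not name the December-March item as the count to be modelled.

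On timing, Study Design states that "assessment points will occur at baseline, end of intervention (1-year), and 6 months postintervention". On season, Intervention Condition states: "Indoor tanning increases in December, peaking in March for seasonal tanners".

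The Abstract, Hypotheses and Measures sections all treat tanning as a primary outcome. Sample Size and Power Calculations refers to it once, in passing, as secondary.

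**The concern.** The recall window is part of the definition of a count endpoint. The article fixes that window twice, differently, so this is not a detail left to a fuller analysis plan. Read literally, the Analysis Plan models a variable that the described survey does not produce.

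Unless one window is settled beforehand, it could be chosen after the data are seen. The choice matters because tanning is seasonal: the two windows can cover quite different parts of the year. They also give the final visit different meanings, because a past-year question asked 6 months after a 12-month programme reaches back into the programme.

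**Working it through.** **The plan's own figures.** No figure is stated for the tanning count or its window. The sample size was reproduced to see whether it depends on the window.

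- Inputs (Sample Size and Power Calculations): 50 groups of 25, intraclass correlation 0.05, d = 0.50, two-sided alpha 0.05, 15% minority, 30% loss.
- Design effect = 1 + (25 − 1) × 0.05 = 2.2.
- Noncentrality = 0.50 × √(1250 / (4 × 2.2)) = 5.96. With 48 degrees of freedom the power is about 0.9999, consistent with the claim of well over 0.80.
- Recruitment = 1250 / (0.85 × 0.70) = 2100.8, against 2100 stated.

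The figures reproduce. They rest on a standardised difference, and no recall window enters.

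**Can any described item supply a past-3-month count?**

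- Past-year total: it covers 12 months and says nothing about when the sessions fell. The 3-month part is 3/12 = 25% of the window and cannot be separated out.
- December-March item: a fixed 4-month calendar window. A 3-month look-back lies wholly inside it only for assessments in March, and even then the two periods differ in length.
- Intention item: prospective, so not a count of sessions.

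None does. The 3-month window appears elsewhere only in the description of an earlier trial in the sample-size section. Carry-over from there is possible, but that is inference.

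**What each window covers.** Count months from the start of a group's feed, with the intervention at months 0 to 12 (Content) and follow-ups at months 12 and 18 (Study Design).

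| Visit | Past-year window | Intervention months in it | Past-3-month window | Intervention months in it |
|---|---|---|---|---|
| Month 12 | 0 to 12 | 12 of 12 | 9 to 12 | 3 of 3 |
| Month 18 | 6 to 18 | 6 of 12 (50%) | 15 to 18 | 0 of 3 |

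At month 18 the 6 intervention months in the past-year window are the same months 6 to 12 already reported at month 12.

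**Illustration from the trial's dates.** Results says the first wave began in September 2016. Its month-12 visit falls about September 2017. A 3-month window there is about June to September, wholly outside December-March. At month 18 (about March 2018) the 3-month window is about December to March, the peak. The past-year window at month 12 runs September 2016 to September 2017 and contains all four peak months. Any 12-month window contains each calendar month once.

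**The case against.** The strongest reply is that only a parenthesis conflicts. That largely stands. The model runs unchanged on the past-year count, and the article condenses a survey that is not shown, so a 3-month item may exist undescribed. A reader might infer that the tanning analysis cannot be run at all; the documents support only that no described item yields the variable named.

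A reader might also stack two further complaints.

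- **Seasonal gaps.** A 3-month look-back contains no December-March day for assessments from about 1 July to 1 December, 5 of 12 months (42%). This arises only if the 3-month window governs, and the 42% needs evenly spread waves, which the article does not state. Seasonality Issues already plans adjustment for month of assessment, a December-March item, and surveying of both arms of a wave at the same times.
- **Overlap at month 18.** This arises only if the past-year window governs. The whole of months 6 to 18 is after randomisation and identical in both arms, so the contrast is not biased. Nor does the article claim that this count isolates a post-intervention effect. What survives is a matter of labelling.

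Redesigning the month-18 item is a trade-off, not a correction. A past-6-month question would contain no December-March day for assessments from about 1 October to 1 December. Using the December-March item with post-intervention months as an offset fails for waves starting in about April or May: their latest season falls wholly inside the intervention, leaving zero exposed months and an undefined log offset.

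The schedule is itself not uniform. Sample Size and Power Calculations refers to 6- and 12-month follow-ups, and Mediators to a 6-month one. If these run from baseline, the past-year window at month 6 would span months −6 to 6, half of it before the intervention. The conflict between Measures and the Analysis Plan stands on either schedule.

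**Conclusion.** The contradiction is real and should be corrected before analysis. Primary Outcomes and the Analysis Plan give windows of 12 and 3 months for the same primary outcome, and the second cannot be obtained from the items described. The fault lies in the definition of the endpoint. Model form, sample size and the validity of the between-arm comparison are not in question.

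The conclusion assumes that the article describes every tanning-behaviour item fielded. The 50% figure for the final visit further assumes the Study Design schedule, with follow-ups at months 12 and 18.

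**What to change.** In the Analysis Plan, replace the 3-month window with the past-year count defined under Primary Outcomes. Name the month-12 past-year count as the analysed tanning outcome, for mothers and for daughters, with the baseline past-year count as covariate.

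If the past-year item is kept at the visit 6 months after the intervention, report that result as a cumulative effect over months 6 to 18, half of it intervention time under the Study Design schedule, and not as a purely post-intervention effect.

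If the fielded survey does hold a 3-month item, describe it under Measures and state which count is primary.

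The cost is a few words of analysis text. No new survey item is needed and the stated sample size is unaffected. Keeping one window at all visits also preserves comparability with baseline. The price is reliance on a year's recall, which the article already accepts, citing correlations of 0.77 to 0.86 with diaries for similar measures.

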Health communication that maximizes the effectiveness of indoor tanning policy, including both parental consent and bans, might activate mothers to protect their teen daughters from the harms. The current study fills this gap in the literature by testing a social media–delivered intervention developed to educate mothers and urge them to withhold permission for daughters to indoor tan. Mothers are an important target because their permissiveness and tanning behavior are strong predictors of daughters’ indoor tanning [18,22,31]. For instance, past-year indoor tanning rates are as high as 30% to 55% in teens whose mothers tan indoors [18,22,31]. Teen girls often report initiating indoor tanning with their mothers [35]. Further, girls whose first indoor tanning experience is with their mothers begin at an earlier age, become more habitual tanners, and are more resistant to change [35]. Recent research indicates that well-crafted communication can reduce maternal permissiveness about indoor tanning [36], but such communication has not been tested as a strategy specifically for maximizing indoor tanning policies. This trial leverages both health communication and behavioral strategies to improve the impact of public health policy. A social media campaign for mothers has the potential to reduce not only the prevalence of indoor tanning in adolescent girls but also the incidence of melanoma in young women. If effective, it could also easily and inexpensively be delivered by cancer-related public health organizations, many of which have social media feeds.

The present paper describes the design and methods of a randomized controlled trial of a Facebook-delivered health communication intervention to reduce mothers’ permissiveness regarding their teenage daughters’ use of indoor tanning, reduce their teenage daughters’ perception of their mothers’ permissiveness, and reduce indoor tanning by both mothers and daughters.

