### Hypotheses

The primary hypothesis is that the intervention will significantly reduce mothers’ permissiveness regarding their daughters’ indoor tanning, their daughters’ perception of maternal permissiveness toward indoor tanning, and both mothers’ and daughters’ indoor tanning relative to the control condition. The secondary hypothesis is that a significantly greater number of mothers will support a ban on indoor tanning for minors in the intervention group compared with the control condition.

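### The tanning hypothesis is tested by a two-part model with two treatment effects per respondent, no deciding contrast is fixed, and one of the two compares groups formed after randomization

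*Protocol article*

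**What the plan says.** - **Protocol article, Hypotheses.** The primary hypothesis includes a reduction in mothers' and daughters' "indoor tanning relative to the control condition". It names no parameter: neither the share who tan, nor sessions among those who do, nor mean sessions overall.
- **Analysis Plan.** The article lists specific tests for the primary hypotheses. Permissiveness and petition signing are each regressed once on the treatment indicator. The tanning test is introduced as concerning tanning frequency, and the outcome is a count of sessions. The chosen model, however, "simultaneously models the effect of the intervention on the prevalence and frequency (among tanners) of tanning sessions".
- **Introduction.** A social media campaign for mothers "has the potential to reduce not only the prevalence of indoor tanning in adolescent girls". The trial's own aim, at the end of the same section, is to reduce tanning, without mention of prevalence.
- **Sample Size and Power Calculations.** The tanning effect cited for planning is sessions among indoor tanners. The text then expects a lower frequency here because not everyone tans, which describes a mean over everyone. The only error rate stands in the power assumptions: "Assuming a 2-tailed alpha of 0.05, a moderate effect size of d=0.50, and an intraclass correlation of 0.05 within each Facebook private group".
- **Moderators.** The only multiplicity correction, Holm-Bonferroni, covers exploratory moderator tests.

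**The concern.** One claim per respondent meets two test statistics. The article does not say whether either suffices, both are needed, or they are combined. Two consequences follow.

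First, if either part at P<.05 may be reported as an effect on tanning, the claim has two chances to succeed by luck.

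Second, the two parts are not equivalent evidence. Whether a participant tans at follow-up can itself be changed by the intervention, so tanners in one arm are not a randomized counterpart of tanners in the other. If light tanners quit, those who remain are heavier users, and the among-tanner effect moves the wrong way because of a benefit. The trial could then report fewer tanners and more sessions per tanner on a primary outcome, with no rule for the conclusion.

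**Working it through.** **1. The plan's own figure.** Inputs from Sample Size and Power Calculations: 50 groups of 25, d = 0.50, ICC 0.05, two-sided alpha 0.05.
- SE = √[4 × (0.05 + 0.95/25)/50] = √0.00704 = 0.0839, and d/SE = 5.96.
- Noncentral t with 48 df gives power 0.9999, so the claim of well over 0.80 is reproduced.
- Recruitment: 1250/(0.85 × 0.70) = 2101, against 2100 stated.

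This calculation is for a standardized mean difference. It does not say which part of the tanning model decides.

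**2. Error per respondent if either part counts.** With two tests at 0.05:
- independent statistics: 1 - 0.95² = 0.0975, or 1.95 times 0.05;
- correlated statistics (bivariate normal): 0.096 at correlation 0.2, 0.093 at 0.4 and 0.088 at 0.6.

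Zero-inflated negative binomial models were also simulated under no effect, with treatment in both parts. Count means, dispersions and zero shares were assumed, some settings being tuned to the 31% of girls who tan given under Setting. Clustering was ignored.

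| Setting | Either part rejects | 2-df joint test rejects |
|---|---|---|
| 735 per arm, two settings, 800 runs each | 0.094, 0.094 | 0.046, 0.056 |
| 625 per arm, two settings, 1000 runs each | 0.099, 0.105 | 0.060, 0.051 |

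The Monte Carlo standard error of the either-part rate is about 0.01 (√[0.1 × 0.9/1000] = 0.0095), so these agree with 0.0975. A joint test, or a single named contrast, stays near 0.05.

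**3. How a benefit can look like harm.** Apart from the 31%, all inputs are assumptions: half of tanners are light (2 sessions), half heavy (18 sessions), 40% of light tanners stop, and nobody else changes.
- Control: prevalence 0.31; mean among tanners (2 + 18)/2 = 10; overall mean 0.31 × 10 = 3.10.
- Intervention: light 0.155 × 0.6 = 0.093, heavy 0.155; prevalence 0.248.
- Overall mean: 0.093 × 2 + 0.155 × 18 = 0.186 + 2.790 = 2.976. Mean among tanners: 2.976/0.248 = 12.0.
- Ratios, intervention to control: prevalence 0.248/0.31 = **0.80**; among tanners 12/10 = **1.20**; overall 2.976/3.10 = **0.96**.

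Nobody tans more, yet the among-tanner ratio is above 1.

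**4. Could both parts be significant in opposite directions?** In unclustered simulations of this example, a significant prevalence fall and a significant among-tanner rise occurred together in about 28% to 31% of runs. A different mechanism gave 65% of 300 runs. There the at-risk share fell from 35% to 26% and the count mean rose 1.35 times, with overall means of 0.35 × 8 = 2.80 and 0.26 × 8 × 1.35 = 2.81.

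These percentages only illustrate. With about 29 per group, the design effect is 1 + 28 × 0.05 = 2.4, and power for the prevalence fall in step 3 drops from about 76% to about 40%.

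**The case against.** The strongest reply is that this is an omission. A condensed article may leave the deciding contrast or a joint test to an analysis plan that is not shown, and a zero-inflated model suits a count that is mostly zeros. Part of this stands: the distribution is not the fault. But the article itself sets out the specific test of a primary hypothesis. It gives that test two effects, one of them not a randomized comparison, and labels the hypothesis frequency while also testing prevalence. That goes beyond missing detail.

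The label could be read as making frequency decisive, and the count outcome and planning data lean that way. It does not settle the matter, because the same sentence adds prevalence and the Hypotheses section speaks only of tanning.

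Some stronger readings are tempting but unsupported:
- **The plan doubles its error rate.** This needs an either-part rule, which the article does not state. If both parts were required, or tested jointly, there would be no inflation. The 0.05 is itself a power assumption.
- **Mothers and daughters multiply it further.** This assumes that any one of four coefficients suffices, whereas the hypothesis covers both mothers and daughters and reads more naturally as requiring both.
- **Prevalence is the stated aim and should decide.** The prevalence sentence describes what a campaign might achieve. The trial's aim is to reduce tanning.

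**Conclusion.** The point holds in conditional form. A single primary claim per respondent is tied to two treatment effects, and the text is inconsistent about which decides. If either may carry the claim, the error is up to about 0.10 per respondent instead of 0.05. That size assumes each test holds its own 5% level and the two are at most moderately correlated (0.14 to 0.23 in the 625-per-arm simulations).

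The second problem does not depend on that rule. Frequency among tanners conditions on a status formed after randomization and can rise through benefit. The ratios 0.80, 1.20 and 0.96 show the mechanism under an assumed split chosen to reveal it. They are not a forecast, and the opposite-verdict percentages are not probabilities for this trial.

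Strictly, the zero part of a zero-inflated model describes structural zeros, and its count part also yields zeros. The two coefficients therefore only approximate prevalence and frequency among tanners, which is a further reason to name the contrast.

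**What to change.** In the Analysis Plan, make one contrast per respondent the gate for the tanning hypothesis, at two-sided 0.05. Either of these would do:

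1. The intervention-to-control ratio of overall mean sessions over all randomized participants, derived from the fitted model. With structural-zero probability π and count mean μ, this is [(1 - π₁)μ₁]/[(1 - π₀)μ₀].
2. A single 2-df joint test of the two treatment coefficients, with direction read from that overall ratio.

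Report the prevalence and among-tanner effects as supporting components, and note that the latter is not a randomized comparison.

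This takes one or two sentences and one extra contrast or joint test, with no new data, since session counts are already collected. The cost is slightly less power when only one part changes. Option 1 judges total sessions, so the pattern in step 3 (ratio 0.96) would count as a small effect despite 20% fewer tanners. Option 2 can reject when the parts pull in opposite directions and the overall mean is unchanged (96% of runs in the second mechanism of step 4). If it is chosen, the text should also say what is concluded when the joint test rejects and the ratio is close to 1.
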